### Trial design

TIARA is an open label, single-blind, non-inferiority randomised controlled trial with three parallel treatment groups. The primary endpoint is clinical improvement at seven days. Randomisation is performed 1:1:1 within each school clinic.

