### Sample size

On the assumption of non-inferiority between hygiene measures and topical fusidic acid and between topical hydrogen peroxide and fusidic acid, and a predicted efficacy of fusidic acid of 80%, we require 160 patients in each intervention group. This provides 80% power and a one-sided *α* of 0·05 to show non-inferiority (10% margin) between each group and topical fusidic acid. In order to allow for 10% loss to follow-up and subsequent exclusions, recruitment of 178 participants to each group is required. Subsequent exclusions and loss to follow-up are defined as participants not available for follow-up at day 7 or when two digital images are not available to assess. Estimates of efficacy are extrapolated from published data [6, 19, 20], and the 10% margin was considered a clinically significant difference [21].

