### Allocation concealment mechanisms and implementation

Randomisation is implemented by block randomisation within each participating school, sequence allocation code was written in R [22]. Children are randomly allocated (1:1:1) to topical fusidic acid, topical hydrogen peroxide, or simple hygiene measures. Participating schools are randomised separately to limit bias caused by excess recruitment to any individual arm within a single school*.* Allocation is performed by school nurses using the pre-generated codes contained in sealed, opaque, sequentially numbered envelopes. Both the participant and school nurse are aware of treatment allocation due to the appearance of the study medications (e.g. hydrogen peroxide has a silvery sheen) or lack of study medication in the simple hygiene measure arm. However, investigators, photograph reviewers, and laboratory staff are blinded to allocation.

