### Statistical analyses

For baseline data, d**i**chotomous variables will be summarised as proportions of patients in each treatment group, differences between groups will be assessed using a chi-square statistic, and where small cell sizes (less than 5) are present, a Fisher’s exact test will be used. Continuous variables with an underlying normal distribution will be summarised as mean and standard deviation, and differences between groups will be assessed using Student’s *t*-test. Other distributions will be either transformed if suitable and *t*-tests performed with reporting of geometric means or distributions will be reported as median and interquartile range and differences in groups assessed using Wilcoxon rank non-parametric tests with Hodges-Lehmann estimates and 95% confidence intervals.

Analysis will be performed after completion of recruitment. Both hydrogen peroxide and simple hygiene groups will be compared independently with fusidic acid with 95% confidence interval. Non-inferiority will be defined as a treatment success rate of no more than 10% below that of the fusidic acid success rate. An intention to treat and per protocol analysis will be performed using all patients with available primary outcome data. Patients without primary outcome data or for whom caregivers withdrew consent to participate will not be included in the analysis.

To investigate predictors of treatment success, backwards stepwise random-effects logistic regression will be performed on a priori and other variables identified as different in baseline characteristics between randomisation groups.

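### Randomisation is blocked within school, but the primary comparison names no school term; an unadjusted interval would be valid but slightly too wide if schools differ.

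*Protocol article*

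**What the plan says.** **Design.** Under Trial design: "Randomisation is performed 1:1:1 within each school clinic". Under Allocation concealment mechanisms and implementation: "Randomisation is implemented by block randomisation within each participating school". The stated reason is balance: "Participating schools are randomised separately to limit bias caused by excess recruitment to any individual arm within a single school".

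**Primary analysis.** Under Statistical analyses, the hydrogen peroxide and simple hygiene "groups will be compared independently with fusidic acid with 95% confidence interval". The criterion is: "Non-inferiority will be defined as a treatment success rate of no more than 10% below that of the fusidic acid success rate". No interval method, model or covariate is named. The article does not say that school is included, nor that it is left out.

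**Exploratory analysis.** The same section specifies a random-effects logistic regression, but only for predictors of success, and without naming the grouping factor.

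**Sample size.** The calculation assumes "a predicted efficacy of fusidic acid of 80%, we require 160 patients in each intervention group", and makes no allowance for school in either direction.

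**The concern.** School is the randomisation stratum, and it can plausibly affect the primary endpoint in two ways that the article describes. The unblinded school nurse may stop study medication for deterioration, which counts as failure. The photographs are taken at each clinic, and pairs that cannot be judged also count as failure.

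Blocking within school keeps the arms balanced in every school, so school differences largely cancel out of the estimated risk difference. An unadjusted standard error still contains that between-school variance, so it overstates the uncertainty.

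In a non-inferiority trial, a lower limit that is needlessly low makes it harder to show non-inferiority that is truly there. The section gives random effects to the predictor model and none to the primary comparison, so the text as it stands points towards an unadjusted primary analysis.

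**Working it through.** **Inputs from the article.** Success 80%, taken as equal in both arms (p = 0.80); margin 0.10; n = 160 evaluable per arm. Sample size alpha: "This provides 80% power and a one-sided *α* of 0·05". Analysis: 95% confidence interval, which means one-sided 0.025 if it is two-sided. Both levels are shown.

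**Assumed, because the article gives none.** The between-school share of outcome variance (ICC), the number of schools and the block size.

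**Step 1. The plan's own figure.** n = (z_alpha + z_beta)² × 2p(1−p) / margin².
- One-sided 0.05: (1.645 + 0.842)² × 0.32 / 0.01 = 198 per arm, not 160.
- One-sided 0.025: (1.960 + 0.842)² × 0.32 / 0.01 = 252 per arm.
- The loss-to-follow-up step does reproduce: 160 / 0.90 = 178.
- With 160 per arm, SE = √(0.32/160) = 0.0447. Power is Φ(0.10/0.0447 − 1.645) = 72.3%, or Φ(0.10/0.0447 − 1.960) = 60.9%.

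This shortfall is a separate issue. It matters here only because it sets the baseline.

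**Step 2. Effect of leaving school out.** Write SE₀ = 0.0447 (unadjusted) and SE₁ = SE₀√(1−ICC), the true sampling error after blocking.
- Power, unadjusted: Φ[(0.10 − z·SE₀)/SE₁]
- Power, adjusted: Φ[0.10/SE₁ − z]
- Actual one-sided error, unadjusted: Φ(−z·SE₀/SE₁)

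| ICC | 95% half-width, unadjusted / adjusted (points) | Interval too wide by | Power lost, one-sided 0.05 | Power lost, one-sided 0.025 | Actual error at nominal 0.025 |
|---|---|---|---|---|---|
| 0 | 8.77 / 8.77 | 0 | 0 | 0 | 0.025 |
| 0.02 | 8.77 / 8.68 | 1.0% | 0.6 points | 0.8 points | 0.024 |
| 0.05 | 8.77 / 8.54 | 2.6% | 1.4 points | 1.9 points | 0.022 |
| 0.10 | 8.77 / 8.32 | 5.4% | 2.8 points | 4.0 points | 0.019 |

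Worked line for ICC 0.05 at one-sided 0.05: SE₁ = 0.0447 × √0.95 = 0.0436. Adjusted power is Φ(0.10/0.0436 − 1.645) = 74.2%. Unadjusted power is Φ[(0.10 − 0.0736)/0.0436] = 72.8%. The difference is 1.4 points.

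**Step 3. The same on the logit scale.** With mean success 80% and normally distributed school effects, SDs of 0.5, 0.8 and 1.0 put 3.8%, 9.2% and 13.4% of the variance between schools. Simulated power at one-sided 0.05:

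| Logit SD | Unadjusted | Stratified | Difference | Unadjusted type I error (nominal 0.05) |
|---|---|---|---|---|
| 0.5 | 72.7% | 73.7% | 1.0 | 0.047 |
| 0.8 | 73.2% | 75.8% | 2.6 | 0.042 |
| 1.0 | 73.7% | 77.6% | 3.9 | 0.039 |

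The formulas in Step 2 give the same values at those shares. At SD 0.3 the share is about 1.4% and the loss about 0.4 points.

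**Step 4. Does the adjustment have a cost?** Steps 2 and 3 treat the adjustment as free, which depends on the method. All runs here used 160 per arm.
- *Mantel-Haenszel, many small schools.* With 40 schools and no school effect, its mean SE was 0.0453 against 0.0446 unadjusted; power was 71.3% against 72.3%. At ICC 0.02 its SE was still larger (0.0448 against 0.0445). It became smaller from ICC 0.05 (0.0442 against 0.0445). With 60 schools and no school effect, power was 70.0% against 71.4% in one simulation and 70.5% against 73.1% in another.
- *Random school effect.* A linear random-intercept version, with 15 to 60 schools, changed power by no more than about 0.3 points when there was no school effect. It gained about 1 point at SD 0.5 and 3 to 4 points at SD 1.0.

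**The case against.** **The inference leans on silence.** The article names no interval method, and covariate handling is commonly left to the SAP, which is not shown. This stands in part. A reader might infer that the plan ignores school; the text supports only that no school term is named for the primary comparison, while random effects are named for another analysis in the same section.

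**Nothing invalid follows.** This stands in full. A reader might infer a false-positive risk from ignoring the stratum. The opposite holds: the unadjusted test is conservative, at 0.039 to 0.047 against 0.05 for SDs of 1.0 to 0.5. The article's reason for blocking is balance within a school, and it makes no claim about precision that the analysis then fails to honour.

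**The size is assumed.** This stands. At SD 1.0, 95% of schools would have success rates between about 42% and 97%; at SD 0.5, between about 62% and 92%. Nothing in the article documents such spread. The schools serve similarly disadvantaged areas, and three blinded assessors grade the photographs centrally. Resistance that varies by school is not documented either, and is not relied on here. A reader should therefore not take a loss of power as established.

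**Stratifying can backfire.** This stands for Mantel-Haenszel with many small schools (Step 4), so it would be wrong to say that stratifying costs nothing when schools are alike. It does not stand against the random-effect model, whose cost in that case was negligible.

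**Conclusion.** The point holds as a modest matter of efficiency. Randomisation is blocked by school and the primary comparison, as written, does not use school. If the analysis is in fact unadjusted, its interval is valid but wider than the design requires whenever schools differ.

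At 160 per arm and one-sided 0.05, the loss is about nil for logit SDs of 0 to 0.3, about 1 point of power at 0.5, and 3 to 4 points at 1.0. If the 95% interval is two-sided, the loss is somewhat larger: 0.8 to 4.0 points for ICCs of 0.02 to 0.10, against 0.6 to 2.8 at one-sided 0.05. The direction is secure given blocking within school. The size is not, because the article gives no ICC, number of schools or block size.

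A reader might infer that adjusting for school would restore the stated 80% power. It would not. Even at SD 1.0, adjusted power at one-sided 0.05 is 77.6%, and the gap between 160 and the 198 per arm that the stated inputs require is a separate problem. If the SAP already adjusts the primary risk difference for school, nothing remains to be done.

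**What to change.** Before unblinding, state in the SAP that the primary estimate for each comparison with fusidic acid is a risk difference adjusted for school.
- **Method.** Use a logistic model with treatment and a random school effect, standardised to a marginal risk difference with a matching confidence interval. Judge its lower limit against −10 points.
- **Alternative.** Use a Mantel-Haenszel risk difference only if schools are few, or if small schools are pooled by a rule fixed in advance. With many small schools it can cost about 1 to 2 points of power (2.6 in one 60-school simulation).
- **Supportive.** Report the unadjusted risk difference and interval alongside. Naming the primary one in advance prevents a choice between two intervals after seeing which clears the margin.
- **Description.** Report the number of schools and the numbers per school and arm.

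The cost is SAP wording and a little programming. No extra data or participants are needed, since school is known from the randomisation.

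### The set called intention to treat is a complete-case set, so loss that differs by arm could raise the chance of a false non-inferiority claim

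*Protocol article*

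**What the plan says.** Under Statistical analyses, the protocol article states: "An intention to treat and per protocol analysis will be performed using all patients with available primary outcome data". The next sentence makes the exclusion explicit: "Patients without primary outcome data or for whom caregivers withdrew consent to participate will not be included in the analysis". The Sample size section describes the same losses: "Subsequent exclusions and loss to follow-up are defined as participants not available for follow-up at day 7", or without two images to assess. It allows 10% for them.

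The comparison is a non-inferiority one: "Non-inferiority will be defined as a treatment success rate of no more than 10% below that of the fusidic acid success rate". Each alternative is "compared independently with fusidic acid with 95% confidence interval".

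Other sections bear on who is lost:

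- Primary outcome methods scores several events as failure with no photograph condition: removal by a nurse or general practitioner because of deterioration, and early discontinuation after clinical assessment. It also scores image pairs that the graders cannot judge as failure. The Outcomes section likewise makes deterioration part of the primary outcome.
- Participant timeline lets caregivers withdraw a child at any stage.
- Allocation concealment says that the participant and the school nurse know the allocation. Only investigators, photograph reviewers and laboratory staff are blinded.

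**The concern.** An intention-to-treat analysis keeps every randomised child in the allocated arm. The set described here does not, and the per-protocol set shares the exclusion. Agreement between the two would therefore say nothing about missing outcomes.

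This matters more than usual here. Treatment is open to families, one arm receives no medication, and the planned loss (10%) is as large in percentage points as the margin. If children who did badly leave one of the alternative arms more readily than they leave fusidic acid, that arm's observed success rate rises, and the trial may declare non-inferiority when it should not. The article states this as a rule; it is not a detail left open for an analysis plan.

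**Working it through.** **Inputs from the article.** Fusidic acid success 80%, 160 evaluable and 178 recruited per arm, 10% loss, one-sided α 0.05 (Sample size). Margin 10 points and a 95% interval of unstated sidedness (Statistical analyses). Equal allocation (Trial design). If the interval is two-sided, it corresponds to one-sided 0.025, so both levels are shown.

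**Assumptions not in the article.** True wound-care success of 70% (exactly at the margin), loss by arm, and success among the missing. These are varied.

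**The plan's own figures.** 160/0.90 = 177.8, so 178 reproduces. The 160 does not: (1.645 + 0.842)² × (0.16 + 0.16)/0.10² gives 198. That is a separate matter, and nothing below rests on it.

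**Formulas.** Let p be the true success rate, l the share lost and s the success rate among the lost.

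- Complete-case rate: r = (p − l·s)/(1 − l)
- Observed difference: d = r_W − r_F (wound care minus fusidic acid)
- SE = √[r_F(1 − r_F)/n_F + r_W(1 − r_W)/n_W], with n = 178(1 − l)
- P(non-inferiority declared) = Φ((d + 0.10)/SE − z), with z = 1.645 or 1.960

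**Main case: 10% lost per arm, lost succeed at 80% (fusidic acid) and 40% (wound care).**
r_F = (0.80 − 0.08)/0.90 = 0.800; r_W = (0.70 − 0.04)/0.90 = 0.733; d = −0.067; SE = 0.0471. Then 0.0333/0.0471 = 0.708, so Φ(0.708 − 1.645) = 17.4% and Φ(0.708 − 1.960) = 10.5%.

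**Same loss, 40% among the lost in both arms.**
r_F = (0.80 − 0.04)/0.90 = 0.844; r_W = 0.733; d = −0.111; SE = 0.0452. Then −0.0111/0.0452 = −0.246, so the rates are 2.9% and 1.4%.

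| Lost, fusidic acid / wound care | Success among lost, fusidic acid / wound care | Observed d (points) | False non-inferiority at 0.05 / 0.025 |
|---|---|---|---|
| 10% / 10% | 80% / 70% (random) | −10.0 | 5.0% / 2.5% |
| 10% / 10% | 80% / 40% | −6.7 | 17.4% / 10.5% |
| 10% / 10% | 40% / 40% | −11.1 | 2.9% / 1.4% |
| 10% / 10% | 0% / 0% | −11.1 | 2.8% / 1.3% |
| 8% / 12% | 40% / 35% | −8.7 | 8.7% / 4.7% |
| 5% / 15% | 35% / 35% | −6.2 | 21% / 13% |
| 5% / 15% | 80% / 35% | −3.8 | 38% / 27% |

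With equal loss, d = (true difference − l(s_W − s_F))/(1 − l). At a true difference of −0.10 this is unbiased when s_W − s_F = −0.10. Inflation at equal loss therefore needs the missing wound-care children to do worse than the missing fusidic acid children by more than 10 points.

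**Read the other way.** Suppose 80% against 72% is observed, with 10% missing per arm. With 40% success among missing wound-care children and 80% among missing fusidic acid children, true wound-care success is 0.9 × 0.72 + 0.1 × 0.40 = 68.8%, a deficit of 11.2 points rather than 8.0. With 40% in both arms, fusidic acid becomes 0.9 × 0.80 + 0.1 × 0.40 = 76.0%, and the deficit is 7.2. Holding the fusidic acid figure at 80% and varying wound care over 5–15% missing and 20–60% success gives 8.6 (0.95 × 0.72 + 0.05 × 0.60 = 71.4%) to 15.8 (0.85 × 0.72 + 0.15 × 0.20 = 64.2%).

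**A result that reverses.** With 9 and 27 lost, 135/169 against 121/151 gives +0.3 points and a two-sided 95% lower limit of −8.5: non-inferior. Counting all 178 per arm with missing as failure, 135/178 against 121/178 gives −7.9 points and −17.2: not shown.

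**Rules set side by side.**

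- A child removed for deterioration is a failure under Primary outcome methods. If the caregiver then withdraws consent, Statistical analyses excludes the child.
- Sample size treats missing images as exclusion and makes no exception for children already scored as failures on clinical grounds.
- Ungradable images are failures; absent images lead to exclusion.

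**The case against.** A reader might infer that every child without photographs is dropped. The article does not support that. The exclusion concerns children without primary outcome data, and deterioration is part of that outcome, so a child removed or stopped early on clinical grounds has an outcome without a day 7 image. The nurse's safety check at days 2 to 4, the request that caregivers report worsening, and the voucher for completing the trial also narrow the route by which a worsening child would vanish. This stands, and it confines the exposure to caregiver withdrawal, missed day 7 visits and absent images.

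A reader might also infer that the bias must favour non-inferiority. That is not supported either. The 17% figure needs the missing to be informative in one arm only. Poor outcomes among the missing in both arms, with equal loss, make the analysis slightly conservative. Nothing in the article shows that loss will differ by arm.

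Finally, imputation and tipping-point methods commonly sit in a statistical analysis plan, which is not shown, so their absence is no fault. But the article does more than stay silent: it fixes the exclusion for both analyses and gives one of them a name that does not fit. That part of the point survives.

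**Conclusion.** The point holds in a limited form and should be fixed. The analysis named intention to treat is complete-case, and the per-protocol analysis offers no protection against informative loss.

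At a true deficit of 10 points, false non-inferiority stays at 5% (2.5%) under random loss and falls to about 3% (1.4%) with 10% missing and 40% success among the missing in both arms. It rises to 17.4% (10.5%) when that 40% applies to wound care only and the missing in fusidic acid succeed at 80%. With 5% against 15% loss and 35% success among missing wound-care children, it reaches 21–38% (13–27%). Figures in brackets are for a two-sided 95% interval. All rest on assumed loss by arm and assumed outcomes among the missing, since the article gives only a 10% allowance. Loss that differs by arm is plausible under open allocation, but it is not established.

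**What to change.** 1. Label the present set complete case and keep it as a sensitivity analysis.
2. Define intention to treat as all randomised children in their allocated arm, except where permission to use the data is withdrawn. Distinguish that from stopping follow-up.
3. Impute missing outcomes within arm by multiple imputation from data already collected: baseline, the day 2 check, and the day 7 nurse or caregiver opinion where available. For children who miss day 7 those opinions will usually be missing too, so imputation alone is not enough.
4. Add a tipping-point analysis that varies the missing outcomes separately by arm. Scoring all missing as failure is no substitute. With 10% loss per arm and 80% against 35% success among the lost, it gives 24% / 15% false non-inferiority, against 21% / 13% for complete case. Under random loss it gives 7.6% / 3.9%.
5. Reconcile Sample size, Primary outcome methods and Statistical analyses, so that a child already scored as a failure for deterioration is not later excluded for missing images or for leaving follow-up.

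The cost is revised wording, modest extra analysis and possibly a wider interval.

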## Data collection methods

### Demographic characteristics

Baseline characteristics of participants are collected at the time of randomisation and reported per randomisation group. The following demographic characteristics will be reported: age, gender, ethnicity, weight, history of pre-existing skin disease, allergies, and location of most severe lesion. All data is collected directly onto an electronic database used by school health clinics; additional trial questions have been created and added to this database by the study investigators. An equivalent paper proforma was designed by SP and included in the study materials for use if required.

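### Baseline significance tests between randomised groups supply extra candidates for a stepwise predictor model, so chance picks them and the reported intervals ignore the selection (minor)

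*Protocol article*

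**What the plan says.** The protocol article commits to three linked steps, all under Statistical analyses.

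1. Baseline variables are compared between randomised groups by significance test. For dichotomous variables, "differences between groups will be assessed using a chi-square statistic", with Fisher's exact test for small cells. Normally distributed variables get Student's t-test. For the rest, after transformation or not, the plan uses t-tests or has "differences in groups assessed using Wilcoxon rank non-parametric tests with Hodges-Lehmann estimates and 95% confidence intervals".
2. The result of those tests helps to choose covariates. The regression takes a priori variables together with "other variables identified as different in baseline characteristics between randomisation groups".
3. The model's aim and selection method are given together: "To investigate predictors of treatment success, backwards stepwise random-effects logistic regression will be performed".

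The Demographic characteristics section lists seven baseline items: "age, gender, ethnicity, weight, history of pre-existing skin disease, allergies, and location of most severe lesion". The article names no a priori variables and gives no threshold for calling a variable different. The comparison of each alternative with fusidic acid against the 10% margin is described in its own paragraph, without reference to this model.

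**The concern.** Allocation is 1:1:1 by blocks within school, using sealed, opaque, numbered envelopes. If that works, the null hypothesis of every baseline test is true by design, and a significant result marks a chance imbalance. Imbalance between arms is a relation between a variable and allocation. Being a predictor is a relation between a variable and outcome. The first carries no information about the second, yet the plan uses the first to decide which further variables may be examined for the second.

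Three consequences follow for the predictor analysis:

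- The additional candidates are a chance draw.
- A variable that truly predicts success, but is balanced and not on the a priori list, is not considered.
- Backwards elimination then reports intervals as if the final model had been fixed beforehand. They ignore the selection and are too narrow, and the surviving coefficients tend to lie too far from zero.

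At stake is what a reader may conclude about which children do well. The trial's fusidic acid comparisons themselves are not at stake.

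**Working it through.** The plan gives no figure on this point to reproduce, so the sizes below are illustrations.

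**Inputs.** From the article: seven baseline characteristics, three arms, 160 children per arm for analysis. Assumed: a two-sided 5% threshold (none is stated), independent variables, and none of the seven on the a priori list.

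**Chance that one variable off the a priori list becomes a candidate.** Under randomisation this is the false-positive rate of the baseline test, however strongly the variable predicts outcome.

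- One test across arms: 5%.
- Two comparisons with fusidic acid: 1 − 0.95² = 9.8% if independent. A simulation with 160 per arm, which allows for the shared arm, gave 9.4%.
- All three pairwise comparisons: 12.4% by the same simulation.

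**Chance that at least one of seven is flagged.**

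- One test each: 1 − 0.95⁷ = 1 − 0.698 = 0.302, about 30%.
- Two comparisons each, 14 tests: 1 − 0.95¹⁴ = 1 − 0.488 = 0.512, about 51%. Allowing for the shared arm, the simulation gave 49%, so 51% is an upper figure.

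**Range under other assumptions.**

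- If only four of the seven lie outside the a priori list: 1 − 0.95⁴ = 19% with one test each, and 1 − 0.95⁸ = 34% with two.
- With a 10% threshold, seven variables and one test each: 1 − 0.90⁷ = 52%.
- Age and weight are correlated in children aged 5–13. This lowers the figures somewhat.

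**What elimination does with these candidates.** A simulation used 160 per arm, one true predictor (odds ratio 2 per standard deviation) and six null variables, none a priori. Entry required a 5% result in any of the three pairwise tests, and retention required p < 0.05 in ordinary logistic regression.

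- The true predictor entered in 13% of trials and, once in, was never dropped. It was therefore missed in 87%.
- At least one null variable was retained in 3.6%.

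The 87% applies only to a strong predictor left off the a priori list, so it does not describe the whole plan. What the simulation shows is that entry by this route is at the chance rate even for a strong predictor. The narrowing of the intervals was not sized.

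**The case against.** Several points on the other side are sound.

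- **A priori variables enter regardless of the baseline tests.** A reader who sees only the end of the sentence might infer that all covariates are chosen by chance. The full sentence does not support that; chance governs only the additional ones. Leaving the a priori list to a fuller document is normal for an article and is no fault.
- **No confirmatory result depends on the model.** A reader might infer that the non-inferiority conclusion is affected. The article does not say that this model adjusts the treatment comparison, and predictors appear neither in the two aims nor among the secondary outcomes.
- **Treatment might be eliminated.** A reader might infer this, since backwards selection is stated and no term is said to be protected. But the article does not say whether treatment is a candidate for removal or forced in, and that detail may sit elsewhere.
- **Two-sample tests with three arms.** The t and Wilcoxon tests compare two groups. Pairwise comparisons with fusidic acid would fit the design, and chi-square and Fisher tests handle three groups. This is at most condensed wording.
- **The percentages measure any flag.** They are not the chance of reporting a false predictor, which was 3.6% in the simulation above.
- **Baseline tests can serve as a check on allocation.** That could justify running them, but not using the result to choose covariates.

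What remains is the stated rule itself. It is committed text, not an omission, and an analysis plan consistent with it would carry it forward.

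**Conclusion.** The point holds in limited form and is minor. The article selects additional candidates for a model of treatment success by a criterion unrelated to prognosis, then applies a selection method whose intervals do not reflect that selection. That chance imbalance says nothing about prognosis follows from randomisation alone, provided that allocation was sound. The 30% and 51% figures rest on the assumed 5% threshold, independence and all seven listed variables being outside the a priori list; they show that a chance flag would be common and nothing more. The harm is confined to the exploratory predictor analysis. It justifies a change because the rule is stated, makes that analysis worse and costs almost nothing to replace.

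**What to change.** Under Statistical analyses:

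1. Describe baseline characteristics by group with the summaries already planned, without significance tests.
2. Delete "other variables identified as different in baseline characteristics between randomisation groups" and the conjunction before it, so that only a priori variables remain.
3. Replace backwards selection with one pre-specified model containing treatment, a random effect for school (the unit within which children are randomised) and the a priori covariates. Name those covariates before unblinding and choose them on prognostic grounds from data already collected. Retain every term and report every coefficient with its 95% confidence interval.
4. If baseline fusidic acid susceptibility is among them, define a category for children without *S. aureus*, since susceptibility is tested only on *S. aureus* isolates: for example no *S. aureus*, susceptible, resistant.

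The cost is a change of analysis wording. No new data, sample size or trial procedure is needed, and the primary comparison is untouched.
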